### Outcome measurements

The primary selected outcome of the study is RHI as a vascular function marker, while other markers including vascular function (i.e., fRHI, AI, AI@75, Endothelin-1, NO, ICAM-1, VCAM-1 and VEGF), inflammation (i.e., IL-6, IL-8, and TNF-*α*) and oxidative stress markers (DNA damage), together with circulating levels of (poly)phenols, salicylates, glycaemia and insulin, are included as secondary outcomes to support and validate the study hypothesis.

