### Sample size, randomization, and statistical analysis

The sample size is determined based on previous studies conducted in our laboratories (30–31) and other research groups [26, 28, 45] to test the efficacy of a blueberry consumption on markers of vascular function. Twenty volunteers are enrolled for the study. This number is considered sufficient (alpha = 0.05, 80% power) to determine an increase of 0.30 in the RHI parameter (endothelial function marker) after blueberry intake. This calculation also considers a possible drop out of 25% of the volunteers. Subjects are randomly divided using a computer random number generator. The randomisation and allocation is performed by a person not involved in the trial and blinded to the investigators and researchers involved in samples analysis. The statistical analysis is performed by means of STATISTICA software (Statsoft Inc., Tulsa, OK, US). Only complete data obtained will be analysed. The Shapiro–Wilk test is applied to verify the normal distribution of the variables under study. In particular, the following statistical elaborations are performed to identify significant differences between treatments: (i) the analysis of variance (ANOVA) with repeated measures, (ii) Wilcoxon paired data test, (iii) Linear Mixed Model (LMM) analysis. Furthermore, regression and correlation analyses (Spearman and Kendall test) are carried out to highlight potential associations between vascular activity, and markers of inflammation, vascular function, oxidative stress, other than biochemical and physiological markers. Corrections for potential confounding factors (i.e., age, gender, drugs/medications) are performed. When appropriate, a post-hoc p-value adjustment is performed using the Hochberg-Benjamin correction. Significance is set at p<0.05; significance in the range 0.05 < p < 0.10 is indicated as trend.

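### Three procedures are listed for treatment differences, and neither the test nor the contrast that decides the primary outcome, RHI, is fixed

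*Protocol article*

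**What the plan says.** Under Outcome measurements: "The primary selected outcome of the study is RHI as a vascular function marker". The Discussion adds that vascular function is measured at baseline and at 2 h after each product, so each participant who completes the trial gives four RHI readings.

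Under Sample size, randomization, and statistical analysis:

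- The design target is one comparison: "This number is considered sufficient (alpha = 0.05, 80% power) to determine an increase of 0.30 in the RHI parameter".
- A normality check comes first: "The Shapiro–Wilk test is applied to verify the normal distribution of the variables under study".
- Then "the following statistical elaborations are performed to identify significant differences between treatments: (i) the analysis of variance (ANOVA) with repeated measures", followed by (ii) a paired Wilcoxon test and (iii) a linear mixed model.
- The threshold is common to all: "Significance is set at p<0.05; significance in the range 0.05 < p < 0.10 is indicated as trend".
- A p-value adjustment is made where judged appropriate. It is not linked to RHI or to these three procedures.

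The section does not assign a procedure to RHI, name a contrast or link the normality result to a choice of test.

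**The concern.** RHI carries one hypothesis, but the listed procedures can give several p-values for it, and they need not address the same quantity. A repeated-measures ANOVA offers a treatment main effect, which averages in the pre-dose reading, or a treatment-by-time interaction. A paired Wilcoxon test can be run on 2 h values or on changes. What the mixed model tests depends on terms that are not given. With about 15 completers expected, these results can fall on different sides of 0.05. If the choice is made after the results are seen, the nominal 5% no longer describes the chance of a false positive on the primary outcome. The band reported as a trend adds a second threshold to which the same freedom applies.

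**Working it through.** **Inputs from the article.** "Twenty volunteers are enrolled for the study"; 25% dropout; alpha 0.05; target 0.30; two treatments; two RHI times. Completers: 20 × (1 − 0.25) = 15, and 15/(1 − 0.25) = 20, so the stated number is consistent with 15 completers. No SD for RHI is given, so the sample size itself cannot be rebuilt. This point does not depend on it.

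**What each procedure can test.** Write B0, B2 for baseline and 2 h RHI on blueberry, and C0, C2 on control. Suppose the true effect is 0.30 at 2 h and baselines are equal on average.

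- Change: c = (B2 − B0) − (C2 − C0), mean 0.30. With two treatments, two times and complete data, the ANOVA interaction is the paired t-test on c.
- 2 h value: p = B2 − C2, mean 0.30.
- Main effect: m = (B0 + B2)/2 − (C0 + C2)/2, mean (0 + 0.30)/2 = 0.15.
- Baseline-adjusted: p regressed on sequence and b = B0 − C0; the intercept has mean 0.30.

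**Assumed variances** (not in the article): 50% between subjects, 20% day, 30% residual. Then:

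- Var(c) = 4 × 0.3 = 1.2
- Var(p) = Var(b) = 2 × (0.2 + 0.3) = 1.0
- Cov(b, p) = 2 × 0.2 = 0.4
- Cov(c, p) = 1.0 − 0.4 = 0.6, so corr(c, p) = 0.6/√(1.2 × 1.0) = 0.55
- The adjusted contrast is p − 0.4b, with variance 1 − 0.16 = 0.84. Its covariance with c is also 0.84, so its correlation with c is √(0.84/1.2) = 0.84.

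The contrasts are related but far from interchangeable.

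**Simulation under no effect**, 20,000 trials per setting, with skewed (lognormal) residuals as the alternative to normal. The entry is the chance that at least one listed p-value is below 0.05.

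| Combination | n=15 normal | n=15 skewed | n=20 normal | n=20 skewed |
|---|---|---|---|---|
| All three on change | 6.0% | 5.8% | 6.0% | 5.8% |
| ANOVA interaction, Wilcoxon on change, baseline-adjusted model | 7.9% | 7.5% | 8.1% | 7.9% |
| ANOVA interaction, Wilcoxon on 2 h values, baseline-adjusted model | 9.4% | 9.0% | 9.5% | 9.4% |

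Each test alone rejects in 4.2–5.2%. With different assumptions (n = 15, normal data, baseline and 2 h differences correlated 0 or 0.5, 4,000 runs), the last row becomes 8.6% and 9.9%.

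**Where the excess comes from** (n = 15, normal, unrounded 5.98% and 9.43%). Three tests on one contrast add 5.98 − 5 = 0.98 points. Letting the contrasts differ adds 9.43 − 5.98 = 3.45 points, which is 3.45/4.43 = 78% of the total excess.

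**If Shapiro–Wilk is meant to select the test.** Applied to the paired change and followed by either the t-test or Wilcoxon on that same change, it gave 5.0–5.2%. Applied to the four raw RHI readings, with ANOVA interaction or baseline-adjusted model still open on one branch and 2 h or change values open on the other, it gave 7.5–8.2% (6,000 runs per setting). On raw readings, at least one of the four was rejected in about 18% of runs even when all data were normal; for independent checks the figure is 1 − 0.95⁴ = 18.5%.

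**The case against.** The strongest reply is that the list is a toolkit. The statistical section covers every outcome: the Endo-PAT indices at two times and the blood markers at five. Three procedures for two data structures is not strange, and no sentence says that RHI receives all three. This stands as a caution: several p-values for RHI is an inference. But the article also does not say which tool belongs to RHI.

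Second, the normality sentence comes directly before the list, so the ordinary reading is parametric if normal and Wilcoxon if not. With one contrast, that rule holds about 5%, and this too stands. The rule is not written, however. If granted, it still leaves ANOVA against mixed model, and the contrast within each.

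Third, a journal article condenses, and the full study document (S1 File) is not shown. It may name the primary test. Silence alone would be no finding. Here the article positively gives three procedures one purpose and one threshold, so the point concerns what is stated. If S1 File designates a test, the remedy shrinks to saying so in this section.

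Fourth, the size depends on contrasts that the article does not specify. That is correct, and it is why the range starts at about 6%.

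**Conclusion.** The point holds as a primary analysis left open between listed procedures and, more importantly, between contrasts. If any of the three may count, the type I error for RHI is about 6% with a common change contrast and about 8–10% with differing contrasts. This holds for 15 to 20 completers under the assumed variances and the error distributions tried.

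A reader might infer more, and the documents do not support it:

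- That the 5% level is certainly lost. The article nowhere says that any significant result counts as success, and one unwritten but plausible reading keeps about 5%.
- That the error is 1 − 0.95³ = 14.3%. This needs independent tests, and these are strongly related.
- That figures above 10% apply. Those need more variants per procedure than the three items listed.
- That repeated-measures ANOVA is unsuitable. RHI has two levels per within-subject factor, so sphericity is not in question, and nothing here argues against ANOVA for the blood markers.

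**What to change.** In the statistical section, designate one primary analysis for RHI: the treatment effect on 2 h RHI from a linear mixed model with treatment, period, sequence and visit baseline as fixed terms and subject as random, two-sided 0.05. State that this result alone decides the primary outcome. Label the paired Wilcoxon test and the repeated-measures ANOVA as sensitivity analyses for RHI, and name the contrast that each tests. Check normality on the model residuals or paired differences rather than on the raw variables. The list can stay as it is for the secondary markers.

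The article reports the trial as ongoing, so this can be done before the data are analysed. It costs a few sentences and the freedom to choose among tests afterwards. It needs no new data and no change in conduct. In the simulations any single pre-named test kept its error at 4.2–5.2%.

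### Results with p between 0.05 and 0.10 are labelled a trend for every outcome, RHI included, and multiplicity correction of the supporting secondary outcomes is only conditional

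*Protocol article*

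**What the plan says.** The statistical section of the protocol article (Sample size, randomization, and statistical analysis) contains three statements that bear on this point:

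- The threshold: "Significance is set at p<0.05".
- The next band, in the same sentence: "significance in the range 0.05 < p < 0.10 is indicated as trend". It makes no distinction between primary and secondary outcomes.
- Multiplicity: "When appropriate, a post-hoc p-value adjustment is performed using the Hochberg-Benjamin correction". It does not say what makes the adjustment appropriate.

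The Outcome measurements section names one primary outcome: "The primary selected outcome of the study is RHI as a vascular function marker". The other outcomes "are included as secondary outcomes to support and validate the study hypothesis". They are:

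- eight vascular markers ("fRHI, AI, AI@75, Endothelin-1, NO, ICAM-1, VCAM-1 and VEGF");
- three inflammation markers (IL-6, IL-8, TNF-α);
- DNA damage;
- four further items, "together with circulating levels of (poly)phenols, salicylates, glycaemia and insulin".

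**The concern.** The two halves of the significance sentence do not agree. One fixes the threshold at 0.05. The other uses the word significance for results that miss it and gives them a favourable name. This is a stated rule, so the point does not depend on anything an analysis plan might add.

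The secondary outcomes are not presented as purely descriptive. They are to support and validate the hypothesis, and the Discussion expects the markers in combination to give evidence on mechanism. The Discussion also describes two earlier studies from the same laboratories with no vascular effect but reduced oxidative stress. A null RHI result alongside a few low secondary p-values is therefore foreseeable. Followed as written, the plan would let chance results among many markers be described as significant or as trends. The one safeguard it names could be applied or left out at the analyst's discretion.

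**Working it through.** The plan gives no error rate for the secondary outcomes, so there is no figure of its own to reproduce. The check asks how often a favourable label would appear if blueberry had no effect.

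**Inputs from the protocol article**

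- Threshold 0.05 and upper edge of the trend band 0.10 (statistical section). Sidedness is not stated; two-sided tests are assumed.
- Secondary outcomes (Outcome measurements): 8 vascular + 3 inflammation + 1 DNA damage = 12 effect markers. Adding glycaemia and insulin gives 14. Adding circulating (poly)phenols and salicylates gives 16. A real difference is expected for those last two after blueberry, so a no-effect calculation suits 12 or 14 better than 16.
- Sampling: 13 of the 16 are blood measures with four post-consumption samples (Biological sampling). The other three (fRHI, AI, AI@75) have one post-consumption measurement, at 2 h (Discussion).
- Completers: 20 × (1 − 0.25) = 15.

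**Step 1: one test.** With no effect, p is uniform. P(p<0.05) = 0.05 and P(0.05<p<0.10) = 0.05, so P(p<0.10) = 0.10. The trend label doubles the chance of a labelled null result, for RHI as for any other outcome.

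**Step 2: one unadjusted test per outcome, independent.** P(at least one p<a) = 1 − (1 − a)^m. The expected number is m × a.

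| m | at least one p<0.05 | at least one p<0.10 | expected p<0.05 | expected p<0.10 |
|---|---|---|---|---|
| 12 | 1 − 0.95^12 = 46% | 1 − 0.90^12 = 72% | 0.6 | 1.2 |
| 14 | 1 − 0.95^14 = 51% | 1 − 0.90^14 = 77% | 0.7 | 1.4 |
| 16 | 1 − 0.95^16 = 56% | 1 − 0.90^16 = 81% | 0.8 | 1.6 |

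**Step 3: correlated outcomes.** The article gives no correlations, so these are assumptions. A simulation with no effect used paired t-tests on 15 participants and 4,000 data sets per setting. Correlation was set among the blood markers and among the Endo-PAT indices.

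| Outcomes | Assumed correlation | at least one p<0.05 | at least one p<0.10 |
|---|---|---|---|
| 14 | 0.3 | 48% | 73% |
| 14 | 0.5 | 39% | 63% |
| 16 | 0.3 | 50% | 74% |
| 16 | 0.5 | 43% | 66% |
| 16 | 0.7 | 34% | 56% |

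**Step 4: separate tests at each time point.** The plan does not specify this, so it is an upper scenario only. Without (poly)phenols and salicylates there are 11 × 4 + 3 = 47 tests. If they are independent, 1 − 0.95^47 = 91% and 1 − 0.90^47 = 99%. With assumed correlations of 0.5 between outcomes and 0.5 between times, the simulated figures are about 75% and 93%.

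**Step 5: with the named correction.** Benjamini-Hochberg at 5% across the whole secondary family held the simulated chance of any false finding at 3.5% to 5.4%. This covered 14 to 55 tests (55 = 13 × 4 + 3, all 16 outcomes) and every correlation tried.

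**The case against.** The plan keeps 0.05 as its threshold and gives the next band a different name. It has a single primary outcome and it does name a correction, which restores control when applied to the whole secondary family (step 5). The unadjusted figures therefore show what happens if the correction is left out; they are not the certain result of the plan. Independence is also unrealistic: AI@75 is AI normalised for heart rate, and the blood markers come from the same samples. Defining the family of tests in detail is commonly left to an analysis plan, and its absence here is no fault in itself.

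All of this stands, and it rules out three stronger readings that a reader might infer:

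- *False findings are near-certain.* That needs unadjusted, nearly independent tests at every time point, with trends counted as findings. The article does not say each time point is tested separately. It lists repeated-measures ANOVA and a linear mixed model, either of which can give one overall test per outcome.
- *The correction will be chosen after seeing the results.* The phrase post-hoc may simply mean adjustment of pairwise comparisons that follow an ANOVA. The text supports discretion, not data-driven choice.
- *The primary result is compromised.* Secondary multiplicity does not touch a single test of RHI at 0.05. Only the trend label reaches RHI.

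The objection does not remove the trend clause, which the article states outright, or the conditional trigger. If post-hoc refers only to pairwise comparisons, nothing in the text requires correction across the secondary markers at all.

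**Conclusion.** The point holds as a fault in the stated reporting and multiplicity rules; it leaves the primary test at 0.05 intact. The trend clause contradicts the 0.05 threshold and doubles the chance of a favourable label on any null comparison, from 5% to 10%. With one unadjusted test per outcome and no effect, at least one secondary result below 0.05 has a chance of 46% (12 markers) or 51% (14 outcomes), and at least one below 0.10 has a chance of 72% or 77%, if tests are independent. For 16 outcomes with assumed correlations of 0.3 to 0.7 the ranges are 34–50% and 56–74%. At least one labelled chance result is therefore more likely than not in every setting examined, but far from certain with one test per outcome. These figures rest on no true effect, no adjustment and two-sided tests. The wording should be changed before analysis.

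**What to change.** In the statistical section:

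1. Delete the trend clause. Treat p ≥ 0.05 as non-significant for every outcome, RHI included, and report each treatment comparison as an estimate with its 95% confidence interval.
2. Replace the conditional adjustment with a fixed rule: Benjamini-Hochberg at 5% across the listed secondary effect markers. Use one overall treatment test per marker from the planned repeated-measures model, and state in advance whether glycaemia and insulin belong to the list.
3. Label comparisons at individual time points, and all correlation analyses, as exploratory.

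The RHI test stays as planned. The change is to the wording of the analysis rules; sample size, visits and assays are unaffected. The downside is that fewer secondary results will be called significant, and none will be called a trend. The Trial status section says the trial is ongoing, so the change should be made and dated before the data are analysed.

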### Monitoring

Given the limited objectives and the short-term nature of the intervention, this trial is monitored by the dedicated research team without the use of a formal data monitoring committee and will be performed independently from the sponsor. Data access is restricted to trained staff with unique password protected accounts. Eventual adverse events such as unfavorable and unintended signs, abnormal laboratory findings, and symptoms temporarily associated with the intervention are collected from the time of intervention until the end, whether or not considered related to the intervention study. All adverse events are considered until they are resolved, but adverse effects are unlikely to occur.

### Ethics and dissemination

The study is conducted in accordance with the Declaration of Helsinki and the Data Protection Act. Trial personnel obtain informed consent from all participants prior to inclusion to the study, including consent for the use of data and biological specimens in other ancillary studies. The principal investigator stores informed consent. All subjects must agree to participate voluntarily and are free to withdraw from the study at any time. The study (S1 File) received ethical approval by the Ethics Committee of the University of Milan on the 12 December 2020 (S2 File). The Research Ethics Committee (REC) approval includes the trial protocol, information sheet and consent form. The trial is registered at the International Standard Randomized Controlled Trial Number (ISRCTN18262533, date of registration: 07 May 2021). Any amendment to the protocol and information provided to participants are submitted to the REC for approval prior to implementation. Substantial amendments may only be implemented after written Ethics Committees approval has been obtained, whereas non-substantial amendments can be implemented without written approval from the Ethics Committee. The Principal Investigator (PI) has to ensure that the participant’s privacy is maintained. Data and source documents are stored in such a way that they can be accessed later for the purposes of monitoring or inspection by the Ethics Committee. Public access to data and other materials could be requested to the PI at the end of the study after completion of elaboration and publication of data. At the end of the study, participants can receive a copy of the results of the study from the PI. The results from the trial are submitted for publication in a peer-reviewed journal irrespective of the outcome. Authorship of presentations and reports related to the study are in the name of the collaborative group and the list will be based on the extent of contribution. Results will be also communicated through other dissemination means including relevant scientific conferences.

## Discussion

The prevention of the decline of endothelial function, especially in older subjects, represents an important task in view of CV events prevention. In this context, diet and dietary factors can contribute not only to optimal aging, but they can also play an important role in the preservation of the vascular system. As reported above, diet is a well-known pillar of optimal aging; however, little evidence is available about the effect of bioactive rich-foods (such as polyphenol-rich foods) on vascular function in older subjects. Thus, there is a need for research that pushes towards acquiring solid evidence. The exploitation of well-controlled and specifically targeted dietary intervention trials represents the correct scientific approach for the evaluation of the health promoting properties of food bioactives, overcoming and completing the observations deriving from epidemiological studies and pre-clinical models. On the other hand, human interventions are difficult to implement in practice, as they can be affected by several confounding factors (e.g., environment, diet, lifestyle) and require considerable efforts in terms of organizational skills, in particular when they address specific target populations such as older subjects.

Previous human intervention studies conducted in our laboratories have documented that the intake of a single portion of blueberries (300 g, providing at about 300 mg of ACNs) counteracted (2 hours post consumption) an impairment in vascular function and blood pressure in a group of healthy young smokers with normal endothelial function [30]. In another study, we found that the same blueberry portion increased vascular function in both young smokers and non-smokers with endothelial dysfunction (2 hours from intake) [31]. Conversely, we have shown that a portion of blueberry purée (300 g) did not affect vascular reactivity (measured 1 hour after intake), but reduced oxidative stress, in a group of young healthy volunteers with normal vascular function [46]. Similarly, we could not demonstrate an effect on vascular function and inflammation, while there was a reduction in oxidative stress markers, after a 6-week intervention with a wild blueberry-based drink (250 mL/d, providing 475 mg of ACNs) in adults with CVD risk factors [47].

Within this study, we want to test the hypothesis that the consumption of blueberries can positively affect markers of vascular function in older subjects. Considering that aging is associated with an increased risk of oxidative stress and inflammation, and that these two conditions are crucial in the onset and progression of vascular dysfunction, we want also to ascertain whether the intake of a single blueberry portion can exert a positive modulation on a plethora of direct and indirect markers of oxidative stress and inflammation. Furthermore, since the potential health benefits should be attributed to the absorption of the bioactive compounds, the kinetic of absorption of (poly)phenols and salicylates from blueberries is evaluated. To this aim, a randomized, controlled, crossover post-prandial study is performed in which the absorption of bioactives from the intake of a single portion of blueberries and the effects on metabolic and functional markers (e.g., vascular function, oxidative stress, and inflammation) is evaluated. The exploitation of a crossover design allows us to reduce the interindividual variability of the subjects, with advantages in terms of sample size and control of the experimental plan for potential confounding factors. The intervention is planned at the facilities of the University in a controlled environment in which subjects can rest, comply with the instructions provided and consume the products. The products consist of a serving of blueberries and a control product. The blueberry portion is defined by considering the amount of ACNs present and potentially capable of exerting a beneficial effect, but also that the portion should be easily consumed as part of a balanced diet. Based on our previous studies, the portion should be in the range 250–300 g (raw product) able to provide at least 300 mg of ACNs [30, 31]. The control product consists in a sugar drink (250–300 mL) containing the same sugars and amount present in the blueberries, matching for macronutrients and energy intake. The inclusion of a control drink with these characteristics allows us to maintain a controlled experimental setting. Subjects also have to follow, 3-day before and during the experimentation, specific dietary instructions consisting of a list of foods allowed and not allowed. Furthermore, weighed food diaries are assessed by each volunteer both before and during the intervention to permit an accurate estimation of nutrient intake and to check the compliance with the dietary instructions by maintaining a high degree of control.

The study is performed in two different phases. Phase 1 consists in the evaluation of the absorption of blueberry bioactives, metabolic and functional markers analyzed in the blood samples collected at different time points (time zero (0 h; baseline), 1 h, 1 h 30 min., 2 h and 4 h from the consumption of blueberry or control products) selected by taking into consideration the “regular” pharmacokinetic of ACNs in terms of time of maximum plasma concentration (tmax; at 2 h), peak of maximum plasma concentration (Cmax) and clearance from blood. These times have been selected based on the results of previous studies showing the absorption of ACNs and a modulation of metabolic and functional markers, including oxidative stress and inflammation, in young healthy subjects or subjects with risk factors following the consumption of blueberries and/or blueberry-bioactives [45–49]. Regarding phase 2, the analysis of vascular function is evaluated at baseline and after 2 h from the intake of blueberry and control products. Also in this case, the choice to measure vascular function at 2 h derives from previous observations, performed both in our laboratories and in others, in which a significant increase in RHI was documented at that specific time from the intake of blueberries both in healthy subjects and in those with an endothelial dysfunction or other risk factors [30, 31, 45, 49]. The decision to split the blood samples collection and the analysis of vascular function into two different days was chosen to overcome the overlapping of the two procedures by reducing possible stress conditions to the volunteers, by facilitating the operating procedures and by limiting the occurrence of potential noises that could affect the different evaluations (vascular function and related markers).

As regards the primary outcome, RHI has been identified as a marker of vascular function that reflects endothelial function of the microvasculature (i.e., resistance vessels) [50]. RHI represents an alternative method to flow-mediated dilatation (FMD), the reference method, since it has the advantage of being simple, operator independent, and therefore less prone to operator bias and variability [36, 51]. In addition, RHI has shown a significant correlation (r = 0.55, p < 0.0001) with FMD [52, 53] and it is widely used, alone or in combination with FMD and/or other markers of vascular function, not only for clinical practice but also to study the effect of drugs, supplements, foods and exercise in numerous human interventional trials [54–58]. Regarding the secondary outcomes, a wide range of metabolic and functional markers related to the aging process, and directly and/or indirectly associated to vascular function, has been identified. In particular, glycaemia and insulin are analyzed in order to ascertain the impact of blueberries, as an important source of single sugars, on glucose metabolism and whether the eventual sugar metabolic response is able to influence vascular function. Finally, the analysis of markers of oxidative stress (e.g., DNA damage at cellular levels), inflammation and angiogenesis (e.g., interleukin-6, IL-6; tumor necrosis factor alpha, TNF-*α*; vascular endothelial growth factors; VEGF), adhesion molecules (vascular cell adhesion molecules 1, VCAM-1; intercellular adhesion molecules, ICAM-1), vasoconstrictors and vasodilators (ET-1 and NO, respectively) is useful to verify the contribution of blueberry in their modulation.

This study has some limitations. First, the difficulty of obtaining a real placebo, thus subjects are not blind to the treatment. Second, the relatively small sample size that, however, was defined based on previous studies obtained in different target groups [30, 31, 45] including older subjects [28]. It is noteworthy that the translation to the general older population could be limited since this target is characterized by wide heterogeneity, thus the demonstration in larger groups of volunteers could be recommended. Third, to limit exclusion criteria in order to enroll subjects with phenotypes that are typical of older age, including those presenting hypertension or mild pharmacological treatments even because in the cross over design adopted each subject will serve as their own control (i.e. also maintaining the same pharmacological treatments). In this regard, characteristics of subjects will be duly considered in data interpretation.

The results of the study will be able to provide several important pieces of information. First, to improve knowledge on the absorption of the bioactive compounds in older subjects, on which data are still lacking in literature. Second, to determine whether the intake of blueberries has a beneficial effect on vascular function also in relation to the absorption of its bioactives. Third, to verify the capacity of blueberries to positively modulate metabolic and functional markers, and whether their combination can provide evidence on the mechanisms by which the food/constituent could exert the protective effect. Overall, these results will be pivotal for the development of new dietary approaches in which blueberries and/or blueberry-products can be used, within a healthy dietary pattern, for improving vascular function with a view to promoting healthy aging.
